### The intervention

The Hospital Elder Life Program (HELP) is an innovative program for the prevention of delirium in hospitalized older people. The strengths of the program include the targeted nature of the interventions, early intervention focusing on prevention, well-trained staff dedicated to the program, standardized intervention protocols, tracking of adherence to all protocols, and built-in quality assurance procedures [16]. The four primary goals of the program to prevent delirium are the following: to maintain cognitive and physical functioning of high risk older adults throughout hospitalization, to maximize independence at discharge, to assist with the transition from hospital to home and to prevent unplanned hospital readmissions [31]. The program has four components:

1) ***Protocols targeting risk factors***

The program provides standardized protocols targeted toward six important delirium risk factors. These factors were selected on the basis of evidence of their association with the risk of delirium and because they were amenable to intervention. These risk factors include cognitive impairment, sleep deprivation, immobility, visual impairment, hearing impairment, and dehydration.

2) ***Elderly care nurse practitioner***

The Elderly Care Nurse Practitioner, who will be introduced as part of the program, plays a central role in HELP. The nurse practitioner will provide a baseline geriatric assessment upon admission and during the project, will develop and implement interventions in collaboration with the nursing staff and other disciplines and will include the patients in the process. This nurse will also provide educational programs and bedside teaching for nursing staff and will coordinate interdisciplinary rounds. The nurse practitioner will receive extensive training concerning assessment of the questionnaires and measurements and how to obtain informed consent. The nurse practitioner will work in close collaboration with a geriatrician.

3) ***Trained volunteers***

Trained volunteers are a unique feature of HELP and are innovative in Dutch hospital care. The coordination of all volunteer activities in HELP will be conducted by a specially trained coordinator and the nurse practitioner. The trained volunteers play a crucial, central role in HELP by conducting the interventions directly at the bedside. The volunteers will stimulate patients to eat, drink and walk; read newspapers with the patients, and participate in (word) games and other activities with the patients. The volunteer training consists of classroom instruction that includes didactic training, small group demonstration, role playing and case discussions. Volunteers will communicate with each other, the nurse practitioner and the nurses during each volunteer shift. Volunteers will be additionally coached and trained quarterly with educational sessions and discussion groups.

4) ***Patient-friendly***

HELP is unique in its approach of being patient-friendly by being directed at the wishes and needs of the older patients and in guaranteeing additional psychosocial support. Patients will receive personalized interventions that match their changing needs throughout the course of hospitalization. Enrolled patients will be regularly reassessed by the HELP staff, and nurses and supervised volunteers will administer interventions that are reassigned daily and tracked for adherence.

All HELP protocols, training manuals and procedures are available for on-site registered hospital units wishing to start a HELP site [31]. For this study, all of the materials will be translated and adapted, if necessary, to Dutch in close collaboration with the developer of HELP, [name]. Subtle changes will be made to the program to fit the Dutch hospital care system. In the original HELP manuals, an Elder Life Specialist and an Elder Life Nurse Specialist were involved. For this project, the titles nurse practitioner and volunteer coordinator are used. Table 1[32] provides an comparison of the original HELP protocols and HELP adapted to the Dutch situation.

**Table 1 T1:** Comparison US and Dutch HELP

	**Original HELP protocols**	**HELP in this study**
Goals	Maintain physical and cognitive functioning, maximize independence at discharge, assist with the transition from hospital to home, prevent unplanned readmission.	No adaptation
Screening	ELS within 48 hours	NP within 36 hours
Inclusion criteria	70 years and over, at least one risk factor for delirium present	70 years and over at risk for delirium according to Dutch Safety Management Program
Exclusion criteria	intubation or respiratory isolation, aphasia, terminally ill, severe dementia, respiratory isolation, expected discharge within 48 hours after admission.	Same exclusion criteria except; exclusion when discharge is expected within 24 hours after admission. An added exclusion criterion; a second admission to a participating unit.
Protocols	Daily visitor program, feeding assistance program, early mobilization program, therapeutic activities program.	No adaptation
Volunteer shifts	Ranging from one to three times daily across protocols	Two times daily, one in the morning, one in the evening
HELP staff	Program director: oversees and supervises the entire program within a hospital.	Project leader :oversees all aspects the project within a hospital.
	Elder Life Specialist: responsible for day-to-day operations of the program, patient screening and coordination of the volunteers.	Volunteer coordinator: screens volunteers, makes sure volunteers attend the training, coordinates and provides support volunteers.
		Nurse Practitioners: screen patients, complete instruction forms for volunteers.
	Elder Life Nurse Specialist: clinical assessment and intervention skills, develops and implements practical strategies to prevent cognitive and functional decline, provides education to nursing staff, liaison with other health care specialties.	Nurse Practitioners: complete the measurements on delirium, quality of life, and cognitive function. They are in close contact with the nurses and instruct them when necessary.
	Geriatrician: provides geriatric assessment and consultation upon request, education to physicians, liaison with hospital medical staff	No adaptations
Staff nurses	ELS and ELNS are in contact with the staff nurses.	NP’s and volunteers are in contact with the staff nurses. The volunteers communicate with the staff nurses on patient level at the start and end of their shift.
Outcomes	Advised: brief cognitive screening test, such as SPMSQ, Activities of Daily Living scores, vital status, length of hospital stay, discharge destination, use of home services, hospital costs.	Incidence, duration and severity of delirium, 6-CIT, Activities of Daily Living Scores, diagnosis, length of stay, care consumption after discharge, health care costs, quality of life.

SPMSQ = Short Portable Mental Status Questionnaire [32].

### The implementation

Three months prior to the first hospital unit starting with HELP, all participating units will receive presentations on the content of the study and the measurements. The purpose of this period is to draw attention to the measurements that nursing should use to assess a patient’s risk for delirium. Baseline data will be collected during this time.

As described, every three months, one hospital unit in both hospitals will start the intervention. The four hospital units in both hospitals are comparable. The units that admit the most older patients were chosen. The staff will be made aware of the study’s time schedule and will know when they are in the control or intervention period. Before the unit starts with the intervention, a team of HELP volunteers will be assembled and will receive a two day training program that was specially developed for HELP. The researcher and local project leader will work closely with the volunteer coordinator, the trainers and the head of the hospital unit. The researcher will give regular presentations for the nurses of the hospital unit and will keep the hospitals informed with regular newsletters and messages on the hospitals’ webpages. The doctors, physical therapists and other professionals in the hospital unit will be informed by the project leader.

Each hospital has created a group of experts that gathers approximately every two months to discuss the HELP plans and its progress. This group can consist of the head and nurses of the participating hospital units, a doctor, the volunteer coordinator and the project leader.

### Study procedure

Figure 1 provides an overview of the measurements and questionnaires used during the intervention period of the study. The measurements are the same in the control period, except for the presence of the HELP volunteers. Eligible patients will be approached by the nurse on call for participation within 24-hours after hospital admission, and the nurse practitioner will measure delirium presence, severity and duration as described in the figures. Most of the questionnaires are part of the current hospital care for older people [26].

**Figure 1 F1:**
[figure not shown]
Measurements during the intervention period.

### Ethical considerations

The HELP study has been approved by the Medical Ethics Board of the University Medical Center of Utrecht. Both the Hospital Gelderse Vallei in Ede and Diakonessenhuis in Utrecht and Zeist have reviewed the study protocol. The board concluded that the study was feasible. Informed consent will be obtained, and patients can always decide not to participate. The study is registered in the Netherlands Trial Register (NTR3842).

### Measurements

#### Six-item cognitive impairment test

The Six-Item Cognitive Impairment Test (6-CIT) is a brief cognitive test that correlates well with the Mini-Mental State Examination (MMSE). The use of this test as a screening instrument for older people in hospital care has been studied and compared to the MMSE [32]. The sensitivity and specificity of the 6-CIT were 0.90 and 0.96, respectively, and the positive and negative predictive values were 0.83 and 0.98, respectively. The 6-CIT was chosen over the MMSE because of its short time to administer (2.5 minutes versus 5.8 minutes for the MMSE) and because the 6-CIT does not require good language skills, reading or writing and is not sensitive to educational level [33].

The 6-CIT will be administered by the nurse practitioner within 36 hours after admission, will be used to gather information on cognitive functioning, and can help inform the decision to consider a patient for participation.

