### Study population

Eligible participants are patients ages 70 years and older who are at risk for delirium and are admitted to the cardiology, internal medicine, geriatrics, orthopedics and surgery units of the two hospitals. The Diakonessenhuis is situated in two locations (one in a university city and one in a smaller town nearby), while the Hospital Gelderse Vallei is located in a more rural area.

Eligible patients will be approached by the nurse on call for participation within 24-hours after hospital admission. Inclusion criteria are being 70 years and older, the absence of delirium at hospital admission and being considered at risk for delirium.

To assess whether a patient is at risk for delirium, we use the three questions of the Hospital Safety Program launched in the Netherlands in 2009 that are part of obligatory hospital care. A review of literature was done before choosing these questions [26]. The nurse will assess the risk for delirium in patients 70 years and older with the following questions: “Do you have memory problems?”; “During the past 24-hours, did you need assistance with your daily self-care?”; and “Were you confused during earlier hospital admissions or illnesses?”. When at least one of these questions is answered positively, there is an increased risk of delirium.

Exclusion criteria include a life threatening situation, being in a palliative phase at admission, an expected hospital stay of 24 hours or less, being legally incapable of participating, unable to communicate verbally, or a second hospital admission during the study period. If the patients are transferred to a participating unit, they are treated as a newly admitted patient; if the patients are transferred from a participating unit to a nonparticipating unit, they are excluded from the study.

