In the Netherlands, screening for delirium in older people has been a quality of care indicator of the Dutch Health Care Inspectorate (IGZ) since January 2010. As a result, hospitals are required to report delirium incidence and to develop policies on delirium prevention [26]. Our data collection closely aligns with this quality measure and strengthens the hospitals’ desire to participate. Given the stepped-wedge design and the fact that measurements are part of regular care, the Nurse Practitioners who are responsible for measuring the primary outcome know which patients receive the intervention. The lack of blinding is preempted by written protocols for screening, and diagnosis as well as the highly standardizes intervention. Moreover units are their own controls and at the same time their data can be compared to data of a comparable unit in the other hospital. To overcome the lack of blinding and ensure reliability of the primary outcome much emphasis will be given to training of the Nurse Practitioners. In addition, CAM interrater reliability between the Nurse Practitioners and between the Nurse Practitioner and a geriatrician will be tested regularly during the study. Finally delirium incidence can be compared with historical data of the participating wards using the procedure described by Rubin et al. in 2006.

Although delirium screening is part of regular care, the protocols are not always followed; this study may improve the percentage of screening for delirium. Thus, an increase in the number of patients with delirium risk is expected, most likely resulting in more delirium diagnoses. Three months prior to the start of the study, the researchers will pay close attention to the measurements that should be part of regular care to achieve the same starting point for all units. This coordinated effort will result in reliable baseline data on delirium risk and delirium diagnosis in all participating hospital units. If HELP proves to be effective, the chance of implementation of the protocol is largely due to the alignment of the aims with screening regulations and developments in health care standards.

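### The 6-CIT may influence who takes part, with no cut-off or rule, in the hands of a nurse practitioner who knows the trial phase, although the eligibility criteria contain no cognitive test

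*Protocol article*

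**What the plan says.** Under Study population, eligibility rests on three conditions: "Inclusion criteria are being 70 years and older, the absence of delirium at hospital admission and being considered at risk for delirium". Risk is settled by three screening questions: "When at least one of these questions is answered positively, there is an increased risk of delirium". No cognitive test score appears. The nurse on call approaches patients within 24 hours of admission.

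The section on the Six-item cognitive impairment test adds a further step. "The 6-CIT will be administered by the nurse practitioner within 36 hours after admission", and the result "can help inform the decision to consider a patient for participation". No threshold, direction or decision rule follows.

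On knowledge of the phase, The implementation says that unit staff "will know when they are in the control or intervention period". The Discussion concedes that "the Nurse Practitioners who are responsible for measuring the primary outcome know which patients receive the intervention". The intervention section also has the nurse practitioner trained to obtain informed consent.

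Table 1, in the exclusion row for this study, says "Same exclusion criteria except; exclusion when discharge is expected within 24 hours after admission" and then "An added exclusion criterion; a second admission to a participating unit". The US list that it carries over includes severe dementia, intubation and respiratory isolation.

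**The concern.** In a stepped-wedge trial each ward is its own control. The comparison is fair only if a ward enrols the same kind of patient before and after it crosses over. Here the phase is known when patients are selected, so the usual protection is an eligibility rule that leaves nothing to judgement. The three risk questions come close to that. The 6-CIT clause reopens the decision and does so on cognition, which the protocol lists among six important delirium risk factors and asks about in its first risk question. If low scorers are handled differently in the two phases, underlying delirium risk differs between phases for reasons unrelated to HELP.

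Timing adds to this. The test may come up to 36 hours after admission and the approach within 24, so a score could influence participation after a patient has already been approached.

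**Working it through.** The point disputes no stated figure. It rests on comparing sections, plus an illustration of scale.

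**1. Selection rule**

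| Item | Study population | Six-item cognitive impairment test |
|---|---|---|
| Basis | Age, no delirium at admission, at least one of three questions positive | 6-CIT score may also count |
| Who and when | Nurse on call, within 24 hours | Nurse practitioner, within 36 hours |
| Cut-off | One positive answer | None |

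The second column gives the test a role in selection that the first does not contain. Study procedure says that measurements are the same in the control period, so the test is given in both phases. Nothing says that its result must be used in the same way in both.

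**2. Exclusions**

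| Item | Study population | Table 1, this study |
|---|---|---|
| Severe dementia | Not named; legal incapacity may overlap | Carried over from the US list |
| Intubation | Not named; largely covered by inability to communicate verbally or a life-threatening situation | Carried over |
| Respiratory isolation | Not named, no overlap | Carried over |
| Second admission | Any second hospital admission in the study period | Only to a participating unit |

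Respiratory isolation and the second-admission rule are clear discrepancies. Severe dementia is a partial one. Intubation is hardly one.

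**3. Scale, with assumed inputs**

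The documents give no delirium risk by cognitive status. Assume that 30% of eligible patients are impaired, with a delirium risk of 60%, and that overall risk is 40%, the top of the 10-40% range under Sample size. That section does not state its control rate. A pooled two-proportion formula (two-sided 0.05, power 0.90) returns its 470 per group at 39% versus 29%, and 477 at 40% versus 30%, so 40% is in keeping with it.

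- Risk in the unimpaired: (0.40 - 0.30 x 0.60) / 0.70 = 0.314.
- If a fraction x of impaired patients is passed over in one phase only, incidence in that phase is [0.30(1 - x) x 0.60 + 0.70 x 0.314] / [0.30(1 - x) + 0.70].

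| x | Incidence | Shift from 40% | Shift if all risks are halved (overall 20%) |
|---|---|---|---|
| 0.1 | 39.4% | 0.6 points | 0.3 points |
| 0.2 | 38.7% | 1.3 points | 0.6 points |
| 0.3 | 38.0% | 2.0 points | 1.0 point |

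If the passing over happens in the HELP phase, the shift favours HELP. If it happens in the control phase, the same shift works against HELP.

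**4. Effect of adjustment**

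In this model, risk within each stratum stays at 60% and 31.4% in both phases whatever x is. Comparing phases within strata therefore gives 60 - 60 = 0 and 31.4 - 31.4 = 0: no bias. Bias survives adjustment only if, among patients with the same score, those enrolled in one phase differ in risk from those enrolled in the other. That would require selection on something not recorded, and the documents give no basis for sizing it.

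**The case against.** The strongest reply has four parts.

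- **The clause is permissive and can be read alongside the criteria.** Patients must consent, and those legally incapable are excluded. A brief cognitive test could simply support that judgement, with the operating rule in the full protocol. This is plausible, but the article does not say it. It describes a role in considering patients for participation, not in assessing capacity. The missing cut-off alone could be put down to condensation; a selection role absent from the stated criteria cannot.
- **The analysis may already deal with it.** Statistical analysis plans a multilevel model correcting for baseline characteristics, and the 6-CIT is collected. The covariates are not named, but that choice is commonly left to the analysis plan. This stands. A reader might infer that adjustment is powerless because patients never enrolled cannot be recovered. That goes too far: when selection depends on a measured covariate, an unbiased comparison does not need those patients back.
- **The direction is unknown.** A reader might infer that staff would prefer patients able to work with volunteers, which would favour HELP. The text gives no support for this. HELP targets cognitive impairment, so impaired patients could equally be favoured. Nor does the protocol rank cognitive impairment as the main risk factor; it lists it first of six.
- **The mismatch in exclusions is a different matter.** A reader might infer that the conflicting lists themselves open the trial to recruitment bias. Nothing suggests that either list would be applied differently by phase, so they are an inconsistency to resolve and not evidence of bias.

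The safeguards in the Discussion (written protocols for screening and diagnosis, training, interrater checks on the CAM) are real, but none is described as fixing how the 6-CIT score is used.

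**Conclusion.** The point holds as an avoidable opening for differential selection. An unblinded nurse practitioner may let an unthresholded test score influence participation, and the eligibility section does not provide for it. The documents do not show that bias will occur, in which direction, or how large it would be.

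The 0.3 to 2.0 points above are an illustration resting on an assumed impaired share, assumed risks, an assumed fraction passed over in one phase only, and no adjustment. The upper figure is one fifth of the 10-point design difference, but it should not be read as an estimate of what this plan would produce. Adjusting for the 6-CIT, correctly modelled, would remove the part that depends on the score; selection on unrecorded judgement would remain.

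The discrepancies between Study population and Table 1 are genuine for respiratory isolation and second admission and partial for severe dementia. They are a separate, smaller matter. The change is worth making because it costs almost nothing.

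**What to change.** 1. In the section on the Six-item cognitive impairment test, delete the clause on participation. Alternatively, replace it with one fixed rule, listed under Study population and applied alike in both phases.
2. Name the baseline 6-CIT score as a covariate in the primary multilevel model.
3. Separately, reconcile Study population with the exclusion row of Table 1 on severe dementia, respiratory isolation and the second-admission rule (any hospital admission, or a participating unit only), so that one eligibility list applies throughout the trial.

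The cost is a few lines of wording; the score is already collected. If the clause is deleted, some patients with low scores who might have been passed over will be enrolled when they meet the listed criteria. Counts of at-risk, approached and consenting patients by ward and period would help to show any shift between phases, but they are an optional extra and do not replace items 1 and 2.
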